### Conclusions

It is expected that the study will contribute to evaluating whether reinforcing front-of-package warning labeling with education enhances its effects and makes them more sustainable. Carrying out this study will allow us to propose whether or not it is necessary to develop new intervention strategies related to front-of-package labeling for a better understanding of the population, improved food choices, and better health outcomes.

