On the other hand, children also influence parents’ purchasing decisions, especially when they want to choose unhealthy foods, which is why the influence of front labeling must be studied from both perspectives (ie, children’s and parents’) [11]. To reduce the purchase and consumption of ultraprocessed foods, various marketing strategies have been implemented, especially for products aimed at school children; however, the results have been varied and limited [12,13].

It is known that food packaging has an impact on how children perceive these products. For instance, the use of drawings and bright colors can make them associate the product with something suitable to eat, which is why changes have been made to packaging designs to discourage consumption, mainly by removing cartoon slogans or legends that promote their consumption [14].

Some types of front-of-package labeling guide the daily intake by indicating the proportion (%) of nutrients found in a serving according to the recommended daily intake for adults. This includes the traffic light system, which uses colors (green, yellow, and red) to indicate the amount of nutrients in a product, as well as warning labels, which are black octagonal symbols, which indicate the excess of nutrients, energy, and substances present in the product and are intended to discourage purchase and consumption [15].

Having identified the relationship between packaging and food consumption, it is expected that front-of-package nutritional labels will reduce the consumption of unhealthy foods [16].

Furthermore, it has been documented that another effective strategy to improve food selection is to enhance nutritional education to develop skills to distinguish healthy products from those that are not considered healthy [17].

Mobile nutritional interventions have been observed to reach a broader range of social and demographic groups and can facilitate the selection of healthy foods at the point of purchase, optimizing decision-making times [18].

In Mexico, it is estimated that 78.6% of the Mexican population aged 6 years and older has access to the internet, with 97% connecting through mobile devices. This is why various health institutions have implemented web portals, social networks, and the use of cell phone messages, telephone, and mobile apps for managing, preventing, and treating health-related activities [19-21].

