## Methods

### Recruitment and Study Design

Third-, fourth-, and fifth-grade elementary school students and their caregivers from 4 primary schools—2 public and 2 private schools—in Mexico City will participate in the study. The schools will be chosen by simple random sampling. Schools will be randomized into 2 groups: intervention and control.

After approval from the directors of the primary schools, meetings will be held with parents to invite them to participate; they will be explained the intervention’s objectives, activities, and duration. Parents and schoolchildren will be invited to sign a consent and informed assent, respectively, clarifying that their participation is voluntary, and they may choose to discontinue at any time without affecting their activities at school.

The main question this study aims to answer is the following: What is the effect of a digital educational intervention about front-of-package warning labels on food selection among children attending primary schools in Mexico City, compared to a control group?

Schools will be randomized into 2 groups. In the control group, the dyads (caregiver-schoolchildren), will receive general nutritional education, and in the intervention group, they will also receive guidance on reading labels, which raises awareness about the impact of consuming processed or ultraprocessed foods on health.

The intervention will be carried out via a website [23] (Figure 1) with audiovisual material, and all participants will also be asked to complete a multiple-choice evaluation (5 questions) to ensure a theoretical understanding of the topics. Other measures will include a lunch register, 24-hour dietary recall, a survey of food habits and consumption, a validated food preference questionnaire, anthropometric measurements (eg, weight, height, and waist circumference), a socioeconomic survey, as well as participation in a simulated web-based food and beverage selection and shopping activity. These measures will help assess if the digital educational intervention on front-of-package warning labeling for children and caregivers improves the selection and purchase of foods.

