### Nutritional Education Interventions

The control group and the intervention group in dyads (caregiver-schoolchildren) will receive general nutritional education, and only the intervention group will receive guidance on reading warning labels, which raises awareness about the impact of consuming processed and ultraprocessed foods on health.

On the website, there will be 4 sections. Participants will receive an account and password to access the educational content corresponding to the group they belong, intervention or control group.

The intervention and control groups will have access to the first section, which contains general nutritional education topics. The second section will contain nutritional education topics related to warning labeling, and only the intervention group will have access to it.

Each topic will be presented through videos, released every 15 days, as well as weekly infographics and tips to the caregivers and children via the website. This material will also be sent to the participants’ mobile devices.

The third section will have the “Online shop,” which will be used as part of the food selection evaluation. The fourth section will evaluate theoretical understanding with 5 multiple-choice questions per topic (Figure 2).

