## Discussion

### Expected Outcomes

This protocol aims to study a public health policy in Mexico, which seeks to contribute to improving the health of the Mexican population by facilitating the understanding of nutritional information about ultraprocessed foods and beverages using front-of-package warning labeling. Studying the effects of this intervention on the population is essential for continuing with the initiative, improving it, or considering other measures to achieve the expected health outcomes.

Some studies have been conducted around the world on different types of front labeling, exploring their effectiveness in selecting and purchasing healthier foods.

A study on adults [24] explored the effectiveness of different types of frontal labeling. Participants were given a brief educational session through a smartphone app before being exposed to 2 experimental shopping tasks. The study found that all types of front labeling, after the educational intervention, resulted in better food selection. In Mexico, a study [25] provided guidance on front labeling via video before participants engaged in online food selection, showing positive effects on food selection.

Another study [26] demonstrated that nutritional warning labels with stamps significantly reduced the percentage of participants who selected products with excessive content of at least one nutrient, compared to the control group (62% vs 85%), and a statistically significant difference was observed for participants who selected products with an excess of certain nutrients, such as sugar (*P*<.001), saturated fats (*P*<.001), and sodium (*P*=.01).

A study in the United States [27] targeting parents concluded that warning labels on sugary beverages reduced the purchase of these products for their children. Although the evidence indicates that front-of-package warning labels can improve the selection of foods and beverages, the effects of these labels on the pediatric population and how children influence the selection and purchase of foods in their homes are still unknown.

On the other hand, the guidance received by participants in the aforementioned studies is limited to ensuring understanding of reading the label.

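### The Discussion and Conclusions attribute the result to the warning labels and to continuing the policy, but the design estimates only the added effect of an education module where labels already apply

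*Protocol article*

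**What the plan says.** **Design.** Under Recruitment and Study Design, "Schools will be randomized into 2 groups: intervention and control". The section on the education interventions gives general nutrition education to the dyads of both arms, but "only the intervention group will receive guidance on reading warning labels". The same sentence describes that guidance as something "which raises awareness about the impact of consuming processed and ultraprocessed foods on health", so the module has two contents: how to read the seals, and why such products are harmful.

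**Labels.** The Introduction dates approval of the black-seal standard to 2020, and the Results section expects the study to start in September 2024. The Abstract gives all participants access to one online store. No section describes a version without seals.

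**Question.** The Abstract's Objective, the end of the Introduction and Recruitment and Study Design all ask for the effect of the educational intervention; the last of these adds a comparison with a control group.

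**Conclusions to be drawn.** The Conclusions, and the Abstract's Conclusions in nearly the same terms, speak of "evaluating whether reinforcing front-of-package warning labeling with education enhances its effects". The limitations paragraph of the Discussion likewise asks whether structured education strengthens what the labels do. Expected Outcomes opens by presenting the work as a study of a public health policy and says: "Studying the effects of this intervention on the population is essential for continuing with the initiative". The sentence goes on to name improving the initiative and considering other measures.

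**The concern.** The question posed in the Methods and the conclusions planned in the Discussion are not the same. The Methods ask what the education module does. The Discussion asks what education does to the effect of the labels, and whether the labelling policy should go on. The first is a comparison of two arms. The second compares label effects under two levels of education. The third needs the label effect itself. The last two require some observation without labels.

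The article states in advance what the results will mean, and it addresses policy makers. A higher proportion of unflagged purchases in the intervention arm could be reported as education making the seals work better, although the harm-awareness content could produce the same result without any use of the seals. A null result could be reported as education not helping, although both arms were educated and both may have improved. Either result could be cited for or against keeping the labels, on which the trial has no evidence.

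**Working it through.** The document states no figure on this point, so this is a check of what can be identified, not a calculation.

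**Notation.** Let Y(L,E) be the mean outcome, for example the percentage of flagged products chosen in the online shop. L = 1 if warning labels are present and 0 if not. E = 1 if the label and ultraprocessed-food module is given and 0 if not. General nutrition education is given in every cell.

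**Inputs.**
- Two randomised groups, with no third or factorial arm (Recruitment and Study Design).
- General education common to both arms; the module in one arm only (Nutritional Education Interventions).
- Labels are national policy for both arms before and throughout follow-up (Introduction; Results).
- One shop, with no display that differs by arm or visit (Abstract, Methods; Primary Outcomes, Time Frame).

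**Cells observed.**

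| | E = 0 | E = 1 |
|---|---|---|
| L = 1 | control arm | intervention arm |
| L = 0 | empty | empty |

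**What each claim needs.**
1. *Effect of the module where labels exist:* Y(1,1) − Y(1,0). Both cells are observed, so it is identified. This is what the objective and main question ask.
2. *Effect of the labels:* Y(1,0) − Y(0,0). One cell is empty, so it is not identified. A decision on continuing the policy needs this or something like it.
3. *Education strengthening the labels' effect:* [Y(1,1) − Y(0,1)] − [Y(1,0) − Y(0,0)]. Two cells are empty, so it is not identified.

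**When would (3) equal (1)?** Rearranged, (3) is [Y(1,1) − Y(1,0)] − [Y(0,1) − Y(0,0)]. It reduces to (1) only if Y(0,1) = Y(0,0), that is, if the module does nothing where there are no labels. The module's own content makes that doubtful. Teaching that ultraprocessed products are harmful can lead a child to avoid them without looking at a seal. The outcome under Food and Drink Selection counts flagged products bought and averages their nutrient content; it does not record why a product was chosen.

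**Do the baseline measurements help?** No. They are also taken after the standard came into being, so change from baseline varies education and time, not labels.

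**Role of the shared education.** It is in every cell and drops out of (1). The contrast remains valid, but it measures an increment over general education, not over no education.

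**The case against.** The strongest defence is that the sentence in the Conclusions is hedged and has a plain reading the trial can answer. Where labels are already law, asking whether reinforcing them with education helps is close to asking whether adding label education improves choices. No section names a label-by-education interaction as a target. On that reading, a claim that the trial cannot answer its own question would be too strong, and the documents do not support it: the objective and main question fit the two-arm contrast.

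Three other stronger readings also fail.
- A reader might infer that educating both arms is a flaw, especially since the Introduction says that "another effective strategy to improve food selection is to enhance nutritional education". It is a legitimate active control that helps to isolate the module. The Introduction's remark concerns education that builds skill in telling healthy from unhealthy products, which is at least as close to the module as to the shared content. The documents give no figure for how much of an overall education effect the shared content might deliver, so no dilution can be quantified.
- A reader might infer that the trial has nothing to say to policy. It can inform improving the initiative or developing new strategies, both of which the article names.
- A reader might take it as stated that every participant sees seals in the shop. That is inferred from the national standard and the shared store. The argument does not depend on it, because no variation in label display is described either way.

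What the defence does not cover is the repeated attribution to the labels' effects, in the Abstract's Conclusions, the limitations paragraph and the Conclusions, and the clause on continuing the initiative. The preceding sentence there speaks of the national policy, and no comparison in the trial sets labels against no labels.

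**Conclusion.** The point holds as one about stated inference. The randomised contrast identifies one quantity: the added effect of a combined label and ultraprocessed-food module over general nutrition education, with labels in force. The labels' own effect and any strengthening of it by education are not identified at any sample size. The policy-continuation inference therefore has no support in the design.

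This rests on two readings of the article: that no label-free condition exists in the trial, since none is described, and that the module's harm-awareness content could act without the seals. If the full protocol contains a label-free shopping condition, the first would need revisiting.

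The contrast itself is unaffected. No outcome or analysis has to change, and the objective and main question stand as written. A reader might also infer that a label-free shopping task must be added. It would be needed only if the interaction were the real target, which no section says. The verdict concerns what can be identified, not the precision available from four schools.

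**What to change.** 1. In the Abstract's Conclusions, the limitations paragraph of the Discussion and the Conclusions, replace the wording about enhancing the labels' effects with: *the added effect on food selection of warning-label and ultraprocessed-food education over general nutrition education, where labels are already in force*.
2. In Expected Outcomes, remove the clause on continuing the initiative. Keep those on improving it and on considering other measures.
3. Add one sentence stating that a null result would not show nutrition education to be ineffective, because both arms receive it.

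Leave the objective and main question as they are. The cost is a narrower stated conclusion; design, conduct and participant burden do not change.
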